### - Epidemiology

Few articles have been published on the epidemiology of MD. Great variation exists in the published reports of the prevalence of MD, ranging from 34.5 cases per 100,000 population in Japan (Shojaku 2005) to 46 cases per 100,000 population in Sweden (Stahle 1978). In the United States of America, reported prevalence is much higher: Alexander (Alexander 2010) reports 190 patients per 100,000, Waldislavosky-Waserman (Wladislavosky-Waserman 1984) reports a prevalence of 218 per 100.000. The difference in prevalence might be due to the wide variations in definitions of MD.

In the Netherlands, a population of 60-100 per 100,000 patients is severely impaired (defined as low quality of live) by the disease (Mateijsen, 2001). There seems to be a slight female preponderance, with up to 1.3 times more women affected than men. The disease is more common in adults in their fourth and fifth decade of life (Kotimaki 1999, Perez 2008, Van Esch 2016).

- Current treatment options and guidelines

The treatment of MD both in primary and secondary care setting is focused on the reduction of the frequency and intensity of vertigo attacks. Current treatments have either proven to be ineffective (Betahistin; Adrion 2016), only have a temporary effect (intratympanic dexamethasone injections; McRackan 2014, or methylprednisolone; Patel 2016), or destroy the labyrinth function (intratympanic gentamicin, labyrinthectomy, selective neurectomy; Pullens 2013; Harner 2001, Sennaroglu 2001). Surgical destruction of the labyrinth reduces the episodes of attacks but causes loss of balance as well, due to one dysfunctional labyrinth. Moreover, permanent hearing loss is reported after this treatment.

Recently, an international guideline for the diagnostic work-up and treatment of MD was published (Basura 2020). It recommends step-up treatment, starting with education of patients and discussing diuretics/betahistine. IT corticosteroids are considered optional if patients do not respond to more conservative therapy. A last non-ablative option that can be considered, is endolymphatic sac decompression, however, results from this type of surgery are discordant. If there is no response to non-ablative treatments, treatment with intratympanic gentamicin is recommended, and if the disease remains unmanageable and the patient has nonusable hearing, labyrinthectomy is advised. Patients should also be referred for vestibular rehabilitation therapy in case of chronic balance problems, and clinicians should counsel patients with hearing problems about hearing assistive technology.

In the Netherlands, there are currently no specific guidelines for the treatment of MD. The guideline 'Dizziness in Elderly' of the Dutch ENT Society ('Duizeligheid bij ouderen', NVNKO, 2015) advises to refer the patients to a specialized ENT surgeon. The guidelines 'Dizziness' of the Dutch General Practitioner Society (Bouma 2017) for general practitioners also advises to refer the patient to an ENT surgeon, but only in case of rapid progressive hearing loss or additional complaints such as instability, head ache or persisting tinnitus. There is no guideline from the Dutch ENT society regarding Meniere's disease.

- Endolymphatic sac surgery

Other surgical treatment techniques target the endolymphatic sac (ES). The advantage of these procedures is that they are non-destructive and do therefore not affect the cochlear and vestibular function, thereby preserving hearing and balance. These procedure involve decompression, shunting or drainage of the ES.

Endolymphatic sac decompression (ESD) consists of a mastoidectomy and, after identification of the endolymphatic sac, wide decompression of this structure (Sennaroglu,

2001). ESD has few surgical complications in comparison with the ablative surgery mentioned above. There is no consensus on the effect of decompression. Convert et al (Convert 2006) report improved quality of life after decompression in a case study of 90 subjects after a follow up period of 57.5 months on average.

Drainage or shunting of the endolymphatic sac (ESS) involves identification of the ES, followed by incision of the sac. A shunt is then placed, enabling drainage of the endolymph. There are several studies that were directed to investigate the effectiveness of ESS (Bretlau 1989, Thomsen 1998, Brinson 2007). Bretlau and Thomsen compared ESS to a sham operation; no differences between the groups was observed. Brinson compared ESS to ESD performed on 88 and 108 patients, respectively. He concluded that both procedures are effective

Multiple histological studies refute the rationale of endolymphatic sac surgery. Firstly, Chung et al (2011), performed a histopathological study 15 patients who had undergone ESS. If the endolymphatic sac does indeed have a function in resorption of the endolymph but does so inadequately, ESS and especially ESD would allow expansion of these structures and would therefore diminish hydrops. However, diffuse hydrops on temporal bone was seen in the cochlea, the saccule, the utricle, and the ampulla after ESD. The authors conclude that ESD does not relieve hydrops in patients with Ménière's disease.

In addition, if the ES was responsible for endolymph resorption, an increase of hydrops can be expected after amputation of the ES. However, Linthicum et al. (2011) reported a case in which removal of the ES did not lead to an increase of hydrops, as seen on temporal bone histopathology. In the assessed samples, Reissner's membrane was attached to the spiral ligament in a normal way, without any evidence of hydrops in the cochlea. In conclusion, the role of the ES is not merely absorption of the endolymph and therefore, providing more space to allow dilatation is not the solution for the observed hydrops.

The success rates of these surgical interventions vary between 30-95% (Sennaroglu 2001; Huang 1991; Silverstein 1989, Durland 2005, Pullens 2013; Convert 2006). It should be noted that the natural course of MD is also favourable, and it cannot be determined to what extent this outcome is due to the surgical intervention. Moreover, the placebo effect may play a major role in the relief of complaints, as 70% of MD patients in all groups (all surgical interventions as well as the control groups) experienced some relief of complaints. This either implicates a beneficial effect of any surgical intervention or of any intervention, be it surgical or non-surgical. This was earlier suggested by Thomsen (Thomsen 1981).

The newly published international guideline makes no recommendation regarding the use of endolymphatic sac surgery, 'due to its uncertain benefit and discordant results when comparing small controlled studies and larger and more numerous uncontrolled studies' (Basura 2020). However, the guideline acknowledges that is utilized by clinicians.

Data from America, Asia and Europe on decompression have been published (Xu 2020, Kitahara 2014, Bojrab 2018, Convert 2006). However, in Scandinavian countries and the Netherlands, the general view is that these surgeries have never proven to be more effective than placebo surgery, and are therefore not performed as part of usual care.

- Endolymphatic duct blockage

Recently, a new surgical intervention has been studied by Saliba et al. (Saliba 2015). A paradigm shift for the pathophysiological model of MD underlies this new treatment. Until now it is believed that the disease is caused by a surplus of endolymph originating in the inner ear, caused by a disequilibrium in the production of endolymph in the inner ear and its resorption in the endolymphatic sac (Merchant, 2005, Semaan, 2010, Salt, 2010). However, Saliba et al. state that the organic substrate of the disease - the surplus of endolymph causing the hydrops – also originates in the endolymphatic sac (ES).

The idea that the surplus of endolymph originates in the ES, is supported by two studies that suggest that the ES has secretory functions as well, rather than merely a function in absorption. In a study of the subcellular structure of the endolymphatic sac in guinea pigs by Takumida et al (1987), the presence of dark cells in the endolymphatic sac was shown. These cells have a secretory role. Moreover, a study performed by Friis (2013) on Lewis rats showed hyperactivity of the cells of the endolymphatic sac, leading to an increase of endolymph secretion.

In conclusion, histological evidence that the ES is –at least in part- responsible for the endolymph surplus.

Based on these findings, Saliba's hypothesis is that in Ménière's disease, there is imbalance in the fluid homeostasis of the endolymph at the level of the endolymphatic sac. He argues there is an increased secretion outweighing a decreased absorption in the ES, leading to increased pressure in the inner ear. Thus, by blocking the endolymphatic duct, Saliba aims to decrease the volume of endolymph in the inner ear, thereby alleviating the symptoms of Ménière's disease.

This operation, referred to as the Endolymphatic Duct Blockage (EDB), involves placing a clip on the endolymphatic duct to separate the endolymphatic sac from the vestibulum and

the rest of the inner ear. Blockage of the endolymphatic duct impedes accumulation of endolymph in the inner ear, and therefore of vertigo attacks. Benefits of this technique are its permanent nature and the fact that it does not destroy the labyrinth or inner ear function.

Saliba (Saliba 2015) has performed a randomized trial to study the effect of EDB. The trial compared EDB to ESD and was conducted prospectively and non-blinded. There was no comparison to a group of patients receiving placebo treatment, for instance a sham operation. The results have been published in 2015 (Saliba 2015) and show that 34 of 35 treated patients were free of vertigo attacks after EDB surgery. It is interesting to note that the efficacy for the absence of vertigo attacks following ESD was only reported to be about 40% in Saliba's trial (Saliba 2015). In earlier studies by Bretlau and later Thomsen, percentages for both ESD and sham operations were reported to be as high as 70%. Possibly, this can be explained by the open character of the Saliba study, causing patients to experience the 'nocebo-effect', caused by feeling like they have not been treated because they did not have the EDB surgery (but the ESD instead). The fact that Saliba et al. did not assess outcomes in a double-blinded way is a fatal flaw in methodology given the high placebo effect of interventions in Ménière disease. Moreover, randomisation was not stratified and there is a risk of recall bias, as it is not described how vertigo bouts are recorded. Lastly, all participants were asked to follow the CATS (caffeine, alcohol, theophylline and salt restricted diet). The role of this diet is not clear.

In a more recent publication by the group of Saliba (Gabra 2016) it is reported that 43 (79%) of a group of 54 patients treated with EDB had an improved quality of life (QoL). The results of these studies indicate that EDB may have a favourable effect on both the bouts of vertigo that MD patients suffer, as on the quality of life.

It should be noted that this study was at risk for recall bias, as patients had to fill out questionnaire in retrospect.

[name] (ENT surgeon, HagaZiekenhuis, The Hague) and [name] (ENT surgeon, Bergman Clinics, Rijswijk) visited Saliba in Montreal to learn this surgical technique. In a pilot group of 34 patients, EDB was performed by [name] in Antwerp. The surgery was performed in Belgium because EDB is not a validated technique in the Netherlands. Therefore, performing this surgery in the Netherlands is not possible. In Belgium however, this surgery is allowed but not covered by the health insurances. Patients can have this surgery if they pay the costs themselves. In this group of 34 patients, a significant ( $p=.001$ ) improvement of quality of life seen. Three of these 34 patients suffered drop attacks post-operatively, but these symptoms

were all resolved in 8 weeks. In three patients, a postsurgical cerebrospinal fluid (CSF) leakage occurred; successful surgical reintervention was performed the next day. In addition, EDB surgery was performed on another group of 32 patients by [name] in Antwerp. No adverse events occurred in this group of patients.

According to the results of Saliba and [name], EDB seems to be a promising surgical technique for treating MD that preserves hearing and equilibrium functions. [name] and [name] felt obliged to further investigate the effectiveness of the EDB in treating MD with the aim to evaluate this surgery in the Netherlands, and set up this trial in cooperation with [name].

The objective of this study is to evaluate the effectiveness of EDB surgery for patients with MD, as compared to a similar intervention, endolymphatic sac decompression. We hypothesize that the number of patients without vertigo spells at 12 months follow up will be higher in the group that has undergone EDB than in the decompression group. Secondary outcomes are defined as minimally clinically significant differences in cumulative incidence of vertigo bouts, hearing, use of escape medication, co-interventions, complications of surgery, questionnaire outcomes (FLS, DHI, THI, SF-36, EQ-5D VAS, iPCQ, iMCQ), CEA, BIA, endolymphatic hydrops on MRI and physiotherapeutical outcomes. We hypothesize that the outcomes of these measures will be better in participants undergoing EDB compared to participants who have had a decompression operation.

## **2. OBJECTIVES**

### **Primary objective**

We will assess whether EDB surgery will result in a significant reduction in the number of patients without vertigo spells at 12 months follow up, compared to patients who undergo a decompression operation.

### **Secondary objectives**

We will determine whether EDB surgery compared to a decompression operation during the 1-year follow up period has a beneficial effect on:

- Cumulative incidence of vertigo bouts
- Hearing
- Use of escape medication (including intratympanic injections)
- Co-interventions (ablative procedure)
- Complications of surgery
- FLS
- DHI
- THI
- SF-36
- EQ-5D VAS
- CEA
- iPCQ
- iMCQ
- BIA
- Endolymphatic hydrops and perilymph signal intensity on MRI
- Physiotherapeutical outcomes: balance, gait, visual acuity

### 3. STUDY DESIGN

The EDB trial is designed as a multicentre, randomized, double blind trial to compare the effectiveness of EDB surgery with decompression surgery in number of patients who are free of vertigo attacks at 12 months follow-up.

- Duration of the study

Total duration of the study is 4 years. In the first 6 months the study will be started, followed by a 2-year period for inclusion and another year for follow up. Analysis of the results will take 6 months. One year after surgery of the last included patient, randomization can be unblinded. In case of a favourable result of EDB, patients in the decompression group will be offered re-surgery to perform EDB if they still suffer attacks. This surgery will be performed within one year after deblinding. In case of a favourable outcome a trajectory for implementation in the current Dutch health care system is also foreseen. Within six months after completion of the study, Zorginstituut Nederland (ZIN) will evaluate the results and decide if the intervention should be implemented in Dutch health care.

- Justification of the design

Three initiating centres (ICs) and four participating centres (PCs) will include patients. A large number of participating centres is chosen to enable rapid inclusion of the required number of participants. As the study ends one year after surgery of the last participant included, it is important to limit the time between surgery of the first participant and last participant. This so to be able to offer the EDB to the decompression group participants who still suffer attacks within a reasonable time span in case of an outcome favourable for EDB. The multicentre design of the study facilitates fast adoption and dissemination of the surgical technique in case of a favourable outcome of EDB.

Endolymphatic sac decompression was chosen as control intervention because the procedure is very similar to EDB. When performing EDB, the same area is exposed and decompression to allow placement of the clip. Because there is no consensus about the effectiveness of decompression, research on this intervention is justified.

The placebo effect plays an important role in the treatment of MD; 70% of the patients experience improvement after any surgical intervention (Thomsen 1981, Bretlau 1989, Thomsen 1998, Pullens 2013). However, because the interventions are equal in intensity, i.e. surgical treatments. Therefore we do expect similar placebo effects in the groups.

- Flow chart

Patients will be included in one of the 7 centres that take part in this study. There will be baseline questionnaires, imaging and testing. There will be a standard preoperative screening by the anaesthetist. The surgery will take place in the centre where the patient is included and where the follow up takes place, unless the local researcher prefers to perform surgery in the HagaHospital (due to experience with the surgery).

After surgery, there will be follow up visit at 1 week, 3 months, 6 months and 12 months after surgery. Throughout this period, patients will continuously report daily functioning and vertigo attacks in the DizzyQuest app. Moreover, the patient is treated by a vestibular therapist in the first 3 months after surgery.

After one year of follow up, both patient and the follow up ENT-surgeon are deblinded. If the patient was allocated to the EDB group, a CT-scan will be performed to assess if the clip is correctly in place if the patient still suffers attacks.

If the results of this trial are in favour of EDB, patients in the decompression group who still suffer vertigo attacks will be offered EDB when the last patient has been deblinded.

An extensive flow chart, including all the questionnaires and tests that will be performed, can be found in the appendix (Appendix 2).

## 4. STUDY POPULATION

### 4.1 Population (base)

Patients with MD will be recruited in all 7 centres. These patients will typically be under treatment by one of the participating centres. Those patients meeting the inclusion/exclusion criteria will be informed by their ENT-surgeon. Below an estimate is provided per centre of the number of patients eligible for this study based on historic data.

| Centre                                               | Expected number of patients eligible for study |
|------------------------------------------------------|------------------------------------------------|
| Beatrix Ziekenhuis, Gorinchem                        | 2                                              |
| Gelre Ziekenhuizen - Apeldoorns Duizeligheidscentrum | 2                                              |
| HagaZiekenhuis Den Haag                              | 62                                             |
| Leids Universitair Medisch Centrum                   | 2                                              |
| Maastricht UMC                                       | 2                                              |
| Medisch Centrum Leeuwarden                           | 1                                              |
| Wilhelmina Ziekenhuis Assen                          | 3                                              |

Based on these estimates, we expect to be able to recruit the total number of 74 patients within the 2 years in which inclusion is planned. There will not be a set number of inclusion per centre: inclusion will happen according to 'first come first serve' principle, which means that inclusion will be competitive.

### 4.2 Inclusion criteria

In order to be eligible to participate in this study, a patient must meet all of the following criteria:

- Definite unilateral MD according to diagnostic criteria of the Bárány Society (Lopez-Escamez, 2016)
- More than 3 patient reported attacks in the 6 months prior to inclusion and at least 1 attack in the 2 months prior to inclusion
- Age  $\geq$  18 years at the start of the trial
- Non responding to a sufficient extent to conservative medical treatment including at least two sessions of at least one intra-tympanic injection (IT) each with corticosteroids (dexamethasone, methylprednisolone, triamcinolonacetonide)
- Dutch health care insurance

Definite MD according to Bárány Society:

- Two or more spontaneous episodes of vertigo, each lasting 20 minutes to 12 hours,

AND

- Audiometrically documented low- to medium-frequency sensorineural hearing loss\* in one ear, defining the affected ear on at least one occasion before, during or after one of the episodes of vertigo,

AND

- Fluctuating aural symptoms (hearing, tinnitus, or fullness) in affected ear (not better accounted for by another vestibular diagnosis).

\*Low frequency sensorineural hearing loss is defined as increases in pure tone thresholds for bone-conducted sound that are higher (i.e. worse) in the affected ear than the contralateral ear by at least 30 dB HL at each of two contiguous frequencies below 2000 Hz

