## 1. INTRODUCTION AND RATIONALE

### - Ménière's disease

Ménière's disease (MD) is an incapacitating disease of recurrent vertigo attacks, accompanied by hearing loss, tinnitus and/or aural fullness. Between the attacks of vertigo intervals of days, weeks or even months may occur (Lopez 2015, Pullens 2013). The natural course of MD has been studied and it has been found that the attacks of vertigo become less severe and disappear after two years in 60% and after eight years in 80% of patients (Portmann 1980; Silverstein 1989, Perez 2008, Van Esch 2016). In the end phase of the disease patients without vertigo attacks may still suffer from lasting hearing loss and tinnitus and chronic instability caused by hypofunction of the labyrinth. Significant comorbidity is seen in patients with Ménière's disease. The most important comorbidities that may also cause dizziness are anxiety disorders and BPPV (van Esch, 2016).

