#### **4.3 Exclusion criteria**

A potential subject who meets any of the following criteria will be excluded from participation in this study:

- Severe disability (e.g. neurological, orthopedic, cardiovascular) according to the investigator, pregnancy or serious concurrent illness that might interfere with surgery or follow-up.
- Active additional neuro-otologic disorders that may mimic MD (e.g. vestibular migraine (VM), recurrent vestibulopathy, phobic postural vertigo, vertebro-basilar TIAs, acoustic neuroma, congenital disorders, enlarged vestibular aqueduct (EVA)-like or genetic disorders (like DFNA9), cervicogenic dizziness), based on the complete clinical record.
- Previous ear surgery for MD (IT injection is not an exclusion criterion)
- Language difficulties
- Active otitis media (with or without effusion)
- Unable or unwilling to use DizzyQuest App

- Unable to undergo MRI (such as gadolinium allergy, claustrophobia, implanted non-MRI compatible device of material, BMI)
- Deafness of the contralateral ear

- Rationale inclusion and exclusion

We aim to perform surgery only on patients with an active Ménière's disease. Because both procedures involve surgery with its associated risks, we only want to perform surgery on participants who have had no benefit of conservative medical therapy and IT injection. Moreover, this will reflect the group of patients who will undergo this surgery in usual clinical practice if this trial leads to EDB being a standard procedure. Patients with prior non-ablative surgery like ESD are excluded in order to avoid any influence in the end result. Moreover, we aim to eliminate or at least minimize all factors that might interfere with follow-up. Patients with contralateral deafness are excluded because it is not clear what the effect of EDB on hearing function is.

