|                      | Rinne left            | Positive
Negative                                             |
|                      | Dix Hallpike          | Positive
Negative                                             |
|                      | If positive: side:    | Left
Right                                                    |
|                      | Diadochokinesis       | Normal
Abnormal                                               |
|                      | If abnormal: side     | Left
Right                                                    |
|                      | Eye pursuit movements | Smooth
Abnormal                                               |
|                      | If abnormal: direct   | Left
Right
Up
Down                                      |

An MRI- and CT-scan will be performed and the patient is referred to a vestibular therapist. A PTA, vHIT and calorigram will be performed. Moreover, from the moment of inclusion, the patients starts reporting in de DizzyQuest App. This is a daily questionnaire of 31 questions addressing general functioning. In case of an attack, a short questionnaire is to be filled out. The inclusion and exclusion criteria will be double-checked by the coordinating investigator and if the patient does meet the criteria, the first survey package is sent through email. This survey pack consists of the HADS, DHI, THI, SF-36, EQ-5D VAS, NPQ, VADL, VAP and a questionnaire about expectations of the treatment.

All the pre-operative data is entered in Castor.

 The VAP and VADL are newly developed questionnaires to assess the effect of dizziness and/or balance problems on patients' ability to do things. They are not an outcome measure in this study, but we aim to anticipate on the possibility that the Bárány Society takes the outcomes of questionnaires into account in future studies. These questionnaires are taken for this trial as well, to enable comparison of the results of this study in the future that only use the VAP and the VADL.

In the following weeks, the patient visits the vestibular therapist, who takes the medical history and performs the first measurements. The patient is seen by the anaesthetist for regular pre-operative screening.

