### 10.1 Primary study parameter

The primary outcome is defined as being attack free at 12 months follow-up. The required significance level of findings ( $\alpha$ ) will be equal to or lower than 5%. Any statistical tests will be two-sided. P-values will be presented. Where confidence limits can be estimated, the confidence level will be 95%. All analyses will be performed by intention to treat.

A chi-square test (or Fisher's exact test) will be performed on the primary outcome variable data (number of patients free of vertigo attacks at 12 months post-operatively, in EDB vs endolymphatic sac decompression group).

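### Pre-operative attack frequency is recorded but enters no stated analysis outside imputation, and disease activity is defined at inclusion rather than at surgery

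*Protocol*

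**What the plan says.** **Eligibility.** Protocol section 4.2 requires more than 3 attacks, by the patient's own report, in the 6 months before inclusion and "at least 1 attack in the 2 months prior to inclusion". The rationale in section 4.3 states the purpose: "We aim to perform surgery only on patients with an active Ménière's disease" Section 8.3.1 adds a second reader ("The inclusion and exclusion criteria will be double-checked by the coordinating investigator"), who verifies the same criteria, still dated to inclusion.

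**Surgery and randomisation.** Imaging, vestibular assessment and anaesthetic screening follow inclusion (8.3.1). Under section 5.1, randomisation takes place in theatre once CT confirms the duct and the clip position. No condition concerns attacks, and I found no maximum interval between inclusion and surgery.

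**Data.** Section 8.3.1 says "from the moment of inclusion, the patients starts reporting in de DizzyQuest App". Its baseline table also holds attack counts for the past 6 and past 2 months and a mean monthly number.

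**Analysis.** For the primary outcome, section 10.1 says "A chi-square test (or Fisher's exact test) will be performed on the primary outcome variable data". Section 10.2.2 describes linear mixed models for the secondary outcomes as EDB versus decompression, with no covariate named. Section 10.1.1 lists baseline measurements and daily app data as imputation variables. Section 8.2.1 stratifies randomisation by gender and by disease duration, cut at two years.

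**The concern.** How often a patient had attacks before surgery is a natural candidate to predict attacks afterwards. The trial will hold that information twice, as a recalled count and as a prospective app record. In a trial of 74 the arms can differ noticeably on it by chance, and the stated analyses have no means of correcting for this. Precision that the trial has already paid for is left unused.

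There is also a gap between aim and rule. The protocol wants to operate on active disease, but activity is judged at one time point and the operation happens at another. The Introduction says: "Between the attacks of vertigo intervals of days, weeks or even months may occur" A participant can therefore meet section 4.2, have no attack afterwards, and still be randomised.

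**Working it through.** **1. Which date each rule refers to**

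| Element | Refers to |
|---|---|
| Attack criteria (4.2) and their second check (8.3.1) | inclusion |
| Aim to operate only on active disease (4.3) | surgery |
| Condition for randomisation (5.1) | surgery, anatomy only |
| App attack record (8.3.1) | inclusion onward, so before surgery too |
| Stated analytic use of baseline and app data outside outcome derivation (10.1.1) | imputation |

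**2. Size of chance imbalance**
For any baseline measure with standard deviation SD, ignoring stratification, the standard error of the difference in means is SD × √(2/n).
- n = 37 per arm (4.4): √(2/37) = 0.23 SD; 1.96 × 0.2325 = 0.46 SD.
- n = 32 per arm after the allowed losses: √(2/32) = 0.25 SD; 1.96 × 0.25 = 0.49 SD.

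About one randomisation in twenty would give a larger gap. For a continuous outcome whose correlation with the covariate is r, adjustment multiplies the residual variance by roughly 1 − r². The documents give no r, so the gain cannot be stated.

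**3. The plan's power figure**
Section 4.4 gives 32 per arm for at least 80% power with Fisher's exact test, 95% v 70%, two-sided 5%. Exact enumeration gives 68.0% for Fisher at 32 and 77.6% at 37. The stated 32 matches an uncorrected chi-square test (80.6%). That mismatch is a separate matter; here it means there is little power to spare.

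**4. Dilution, illustration only**
Assume a share q of each arm is in remission at surgery and attack free regardless, and that 95% v 70% applies to the rest. Each arm's rate is q + (1 − q) × planned rate, so the difference is (1 − q) × 25 points.

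| q (assumed) | Rates | Difference | Fisher power, 37 per arm |
|---|---|---|---|
| 0 | 95.0% v 70.0% | 25.0 | 77.6% |
| 5% | 95.3% v 71.5% | 23.8 | 74.2% |
| 10% | 95.5% v 73.0% | 22.5 | 70.4% |
| 20% | 96.0% v 76.0% | 20.0 | 61.5% |
| 30% | 96.5% v 79.0% | 17.5 | 51.1% |

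The planned rates may already include remission. With q = 20% and 93.75% v 62.5% among active patients, 0.20 + 0.80 × 0.9375 = 95% and 0.20 + 0.80 × 0.625 = 70%. That is exactly the planned contrast, with no loss against plan.

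**5. Information available for adjusting the primary outcome**
Expected failures: 37 × 0.05 = 1.85 with EDB and 37 × 0.30 = 11.1 with decompression, about 13 in total. The chance of no failure at all in the EDB arm is 0.95^37 = 15%, in which case ordinary logistic regression gives no finite treatment estimate.

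**The case against.** **The unadjusted test is valid.** This stands. Randomisation protects the comparison, chance imbalance is not bias, and any remission falls on both arms alike. The point concerns precision and interpretation.

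**Covariates and supportive analyses can be left to an SAP.** Largely fair, as the SAP is not shown and may settle this. But the protocol itself fixes an unadjusted primary test and describes the secondary models by treatment group alone, so the addition is worth making where those statements stand.

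**Natural course is already handled by stratification (8.2.1).** Partly. It balances disease duration in two categories. It does not balance attack frequency within those categories.

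**A short app window may be noisier than the 6-month count.** This stands and shapes the fix.

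**A reader might infer that power falls to between 51% and 74%.** The documents do not support this. The share in remission is unknown, and section 4.4 takes its rates from operated series whose success, the Introduction says, cannot be separated from the favourable natural course. The Introduction's figure of 60% without attacks after two years is general natural history. It is not a rate over a pre-operative wait of weeks in patients selected for recent attacks.

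**A reader might infer that surgery should wait for a fresh attack.** The documents do not support this either, because a quiet spell is not remission. The minimum eligible rate is 4 attacks in 6 months, or 4/6 × 2 = 1.33 per 2 months. Assuming Poisson attacks at that unchanged rate, exp(−1.33) = 26% of still-active patients would have none in a given 2 months. The expected eligible pool in section 4.1 is 74, exactly the target, so there is no surplus to absorb deferrals.

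**Conclusion.** The point holds in a limited form. Pre-operative attack frequency is collected, but outside imputation no stated analysis uses it. With 37 per arm, a chance gap of up to about 0.46 SD would be unremarkable and uncorrected. The consequence is lost precision and a harder reading of the attack outcomes, not systematic bias. The gain from adjustment depends on a correlation that the documents do not give.

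The eligibility gap is real in the text: activity is tied to inclusion, the aim to surgery, and nothing visible connects them. Its effect on the contrast cannot be sized. A reader might also infer that activity is checked only once or that app data go unused. In fact a second person verifies the criteria, and app data feed the imputation and the outcome itself.

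Two limits apply: the visit flow chart in Appendix 2 was not in the text available, so a maximum interval stated there cannot be excluded; and the imbalance figures ignore stratification.

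**What to change.** **Section 10.2.2:** include pre-operative attack frequency as a covariate in the analysis of cumulative incidence of vertigo bouts. Use the app rate from inclusion to surgery together with the 6-month count from the baseline table, or the count alone when the app window is short. State in advance what counts as short.

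**Section 10.1:** keep the unadjusted test as primary. Add one pre-specified supportive analysis of the primary outcome adjusted for the same measure. With about 13 expected failures, limit it to this one covariate or use a penalised model, which also copes with an arm that has no failures.

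**Sections 4.2, 4.3 and 5.1:** reconcile the aim of operating only on active disease with the inclusion-dated criteria and the anatomical condition for randomisation. How this is done is for the sponsor; no deferral rule is proposed here.

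**Cost:** the analysis changes need wording only, since the data are already collected and precede randomisation. The reconciliation is a short text amendment.
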